Regarding the participants’ adherence, to ensure that they carry out the protocols and that they are executed properly, the supervised session will be carried out first. Other measures adopted by the researchers will be: (I) guidance after the supervised session on how the unsupervised sessions should take place; (II) give a copy of Table 1 containing information’s regarding the program and showing how unsupervised sessions should take place; (III): daily text message on the participants’ phone advising them on how the sessions should take place; (IV) inform the participants that they can contact the researchers to answer questions about the protocol.

Participants will be allowed to continue performing running activities during the study. There will be no need for the presence of a data monitoring committee or interim analyses and audits in order to determine the continuation or end of the study as the time for executing the protocol/study is short and the risks offered by it are minimal. The monitoring of possible adverse events will be done daily during the protocol period, any participant who reports pain worsening or other musculoskeletal pain will be instructed to reduce their training volume. The adverse effects will be addressed descriptively in the study results. If the pain persists to the point where participation is impossible, the participant will be considered as a drop-out of the intervention because of injury and the previous data collected will be used in the analysis.

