### Outcomes measures (dependent variables)

The primary outcome of the study will be: (I) pain during daily activities (usual)—assessed using the Visual Analog Pain Scale [29]; The secondary outcomes will be: (II) pain during running—assessed using the Visual Analog Pain Scale [29]; (III) function—assessed using the Patellofemoral Disorders Scale [31]; (IV) kinematics of the lower limbs in the frontal (contralateral pelvic drop; hip adduction) [33,35,36] and sagittal planes (foot inclination; tibia inclination; ankle dorsiflexion; knee flexion) [33,37,38]–assessed through digital videos using two webcams (MyoVideo 139 HD Color Webcam) sampling at 30 frames per second and two leds (LED Floodlight) [33]. The video recordings will be analyzed using the MyoResearch 3.14 –MyoVideo software (Noraxon U.S.A. Inc.). The kinematic variables of interest were chosen based on previous studies [14,15,19,47,48]. The systematic review and meta-analysis of Neal and colleagues [14] shows a relationship between increased hip adduction and contralateral pelvic drop with PFP. The study of Wille and colleagues [47] showed that foot inclination angle and peak of knee flexion are variables that may predict knee joint loading and PFJ forces during running. Tibia inclination during initial contact is related with cadence and length [48] and these are associated with PFJ forces [18,19]. For the comparison of the three study subgroups, the average of points on the visual analog scale of pain, average of points on the scale of Patellofemoral disorders and the peak in degrees of the contralateral pelvic drop, hip adduction, knee flexion and ankle dorsiflexion during midstance and foot inclination and tibia inclination during the initial contact will be considered. The three groups will be compared before (t0), immediately after (t2) and six months (t24) after starting the protocol.

Regarding the retention of the participants, to ensure that there are minimal losses during the follow-up period, the researchers will make a monthly phone call to monitor pain, the current level of training, physical activity practice and if the participants sought for other methods of treatment. Participants can withdraw from the study for any reason at any time, in which case the researchers will collect the pain and function outcomes using the aforementioned instruments (if possible) and report the reasons why these patients did not complete the follow-up (Fig 1).

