### Data analysis

The data of each participant will be extracted for SPSS (Statistical Package for Social Sciences) version 23.0 for later statistical analysis. Descriptive analysis will be performed with calculation of means, standard deviations and 95% confidence intervals for quantitative variables and frequencies and percentages for qualitative variables. Data normality and sphericity will be tested using the Shapiro-Wilk and Mauchly’s tests, respectively. Baseline demographic data will be compared using ANOVA (parametric data), Kruskall-Wallis (non-parametric data) and Chi-squared tests. To compare the effects of the rehabilitation programs on the outcomes of the study, a repeated measures ANOVA with a 3-by-3 mixed-model (parametric data) or the Generalized Estimation Equations procedure with gamma distribution model (non-parametric data) will be used. Time (t0 x t2 x t24) will be used as repeated factor, group (impact x cadence x control) as independent factor and the mean of points on the visual analog pain scale, mean of points on the Patellofemoral Disorders Scale, and the peak in degrees of the contralateral pelvic drop, hip adduction, ankle dorsiflexion and knee flexion during midstance, and foot inclination and tibia inclination during initial contact as dependent variables. Baseline characteristics that are different across groups will be included as covariates in the model. Significance level of p <0.05 will be adopted. Sidak’s post-hoc will be used to make pairwise comparisons. Subgroup analysis and adjusted analysis will not be performed. Intention-to-treat analyses will be conducted where the subjects will be analyzed independently of adherence to the protocol or retention in the follow-up.

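### The rule for participants stopped by pain relies on earlier data and is not reconciled with the withdrawal and intention-to-treat rules

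*Protocol article*

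**What the plan says.** Three places in the Protocol article bear on a participant who stops because of pain.

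- **Rehabilitation programs (independent variables).** On safety, "The monitoring of possible adverse events will be done daily during the protocol period". Anyone reporting worse pain, or musculoskeletal pain elsewhere, is first told to cut back training. The rule for stopping begins "If the pain persists to the point where participation is impossible"; that person is then "considered as a drop-out of the intervention because of injury and the previous data collected will be used in the analysis". The section does not say whether the person is still assessed at t2 and t24.
- **Outcomes measures (dependent variables).** A separate rule covers withdrawal from the study, whatever the reason: "in which case the researchers will collect the pain and function outcomes using the aforementioned instruments (if possible"). It gives no time point and does not name kinematics.
- **Data analysis.** "Intention-to-treat analyses will be conducted where the subjects will be analyzed independently of adherence to the protocol or retention in the follow-up". The planned model is "a repeated measures ANOVA with a 3-by-3 mixed-model (parametric data) or the Generalized Estimation Equations procedure with gamma distribution model", with t0, t2 and t24 as the repeated factor.

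**The concern.** Taken at face value, the rules treat two kinds of participant the wrong way round. Someone who leaves the study altogether is approached for pain and function scores. Someone who merely stops the programme because of pain is represented by what was collected before.

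The trigger is pain, and pain is the primary outcome whether one follows the Abstract (pain during running) or the Outcomes measures section (usual pain). Any later values lost under this rule would therefore be missing for a reason tied to the outcome. Group C receives no retraining, so the rule would fall mainly on groups A and B. A poor response to retraining could then appear in the descriptive account of adverse effects but be absent from the efficacy comparison.

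**Working it through.** **1. Which earlier data exist.** Assessments are at t0 (before), t2 (immediately after the two-week programme) and t24 (six months). Daily monitoring runs during the programme. A stop in that period comes before t2, so the earlier scheduled data are t0 alone.

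**2. What an analysis can do with t0 alone.** The article does not say which of these would apply.
- A conventional repeated measures ANOVA needs all three values, so the person is excluded.
- GEE keeps the t0 value but has nothing after baseline from that person.
- Carrying t0 forward records no change for someone whose pain made participation impossible.

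**3. Size of an arm.** The Sample size section gives partial eta squared 0.19, alpha 0.05, power 99%, three groups and three measurements. Not stated and assumed here: correlation 0.5 between measurements, sphericity holding.
- f = √(0.19/0.81) = 0.484; the plan uses 0.48.
- λ = f² × N × m/(1 − ρ) = 0.2304 × 21 × 3/0.5 = 29.03, with 4 and 36 degrees of freedom. Power is 0.990.
- At N = 18 power is 0.973, so 21 is the smallest balanced total reaching 99%. The stated figure reproduces.
- The total of 30 allows for 1 − 21/30 = 30% loss. At 1:1:1 there are 10 per arm, so one participant is 10% of an arm.

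**4. If stoppers are omitted.** Let a fraction p of an arm stop, with pain d points above the rest of that arm, whose mean is c. The full arm mean is (1 − p)c + p(c + d) = c + pd. Omitting the stoppers leaves c, so mean pain is understated by p × d. With d = 3 (assumed):
- 1 of 10: 0.1 × 3 = 0.3 points
- 2 of 10: 0.2 × 3 = 0.6 points
- 3 of 10: 0.3 × 3 = 0.9 points

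Other assumed inputs (completers improve by 2 points, stoppers change by 0 to +2, so d = 2 to 4) give 0.2–0.4, 0.4–0.8 and 0.6–1.2 points for 1, 2 and 3 stoppers.

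**5. If t0 is carried forward.** A stopper whose true change is w is recorded as 0, so the arm mean is off by p × w. With w = 0 there is no error. With w = +2 it is 0.2 to 0.6 points for 1 to 3 stoppers. If stoppers have improved by t24, the error runs against retraining.

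**6. Extreme case.** Simulation with 100,000 draws: no true effect, the worst 1, 2 or 3 of 10 values missing from one retraining arm, none missing from control. The bias is 0.17, 0.32 or 0.46 SD. An unadjusted two-sided 5% t test rejects in 7.4%, 11.7% or 16.8% of trials. This is a deliberately severe pattern and not the planned model, so it marks how bad matters could get, not what to expect.

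**The case against.** A reader might infer that the article discards later data from these participants, that the three rules flatly contradict each other, and that the worst outcomes are certain to vanish from the retraining arms. The text does not support any of these.

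- The article says earlier data will be used. It does not say that later data will not be collected or used. Dropping out of the intervention can mean stopping treatment while follow-up continues, and the sentence can be read as a promise not to delete what is already in hand. Using earlier data is not in itself against intention-to-treat. The rules are unreconciled rather than strictly contradictory.
- Exclusion is one of several possible consequences. Under carry-forward nobody is removed, and GEE still uses t0. Missing-data handling may be set out in an analysis plan that is not shown, and its absence from the article is not the point made here.
- The safety rule is worded for participants in general, without excluding group C. Controls keep running and could also leave because of pain, which would offset the imbalance. The rule also follows mention of musculoskeletal pain elsewhere, and someone stopped by that need not have worse patellofemoral scores.
- The number of stoppers and their excess pain are assumptions. Three of 10 would use an arm's whole share of the 30% loss allowance on pain stops alone. Adverse effects and reasons for non-completion are reported, so harm would not be wholly hidden.

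All of this limits how strongly the point can be put. What remains is that the article states an analysis rule for this group, that its natural reading leaves t0 alone for a stop within the programme, and that nothing ties it to the other two rules.

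**Conclusion.** The point holds as an unreconciled rule that permits a biased reading. If earlier data alone are used for participants stopped by pain, the pain comparison could be biased, probably in favour of retraining, because pain triggers the stop and only groups A and B have a retraining programme to stop. Neither the direction nor the size is established by the article. The illustrative 0.3 to 0.9 VAS points rests on 1 to 3 of 10 being omitted from one arm, a 3-point excess and no matching loss in group C; under carry-forward the error differs and can be nil or reversed. The sample size figure is unaffected. The wording should be settled before outcome data are analysed.

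**What to change.** Reconcile the Rehabilitation programs, Outcomes measures and Data analysis sections with one statement, for example: *A participant who stops the programme because of pain has discontinued the intervention but has not left the trial. In all arms, VAS usual pain, VAS running pain and the Patellofemoral Disorders Scale are still collected at t2 and t24, by telephone if needed, and analysed in the randomised group.*

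The cost is one paragraph and a few extra contacts. Monthly calls that monitor pain are already planned, but they need not coincide with t2 at week two, so contacts have to be timed to t2 and t24. The change concerns data collection and analysis only; when a participant stops is untouched. A sensitivity analysis giving the worst running-pain score to anyone unable to run because of knee pain is optional and is not needed to reconcile the wording.

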### Outcomes measures (dependent variables)

The primary outcome of the study will be: (I) pain during daily activities (usual)—assessed using the Visual Analog Pain Scale [29]; The secondary outcomes will be: (II) pain during running—assessed using the Visual Analog Pain Scale [29]; (III) function—assessed using the Patellofemoral Disorders Scale [31]; (IV) kinematics of the lower limbs in the frontal (contralateral pelvic drop; hip adduction) [33,35,36] and sagittal planes (foot inclination; tibia inclination; ankle dorsiflexion; knee flexion) [33,37,38]–assessed through digital videos using two webcams (MyoVideo 139 HD Color Webcam) sampling at 30 frames per second and two leds (LED Floodlight) [33]. The video recordings will be analyzed using the MyoResearch 3.14 –MyoVideo software (Noraxon U.S.A. Inc.). The kinematic variables of interest were chosen based on previous studies [14,15,19,47,48]. The systematic review and meta-analysis of Neal and colleagues [14] shows a relationship between increased hip adduction and contralateral pelvic drop with PFP. The study of Wille and colleagues [47] showed that foot inclination angle and peak of knee flexion are variables that may predict knee joint loading and PFJ forces during running. Tibia inclination during initial contact is related with cadence and length [48] and these are associated with PFJ forces [18,19]. For the comparison of the three study subgroups, the average of points on the visual analog scale of pain, average of points on the scale of Patellofemoral disorders and the peak in degrees of the contralateral pelvic drop, hip adduction, knee flexion and ankle dorsiflexion during midstance and foot inclination and tibia inclination during the initial contact will be considered. The three groups will be compared before (t0), immediately after (t2) and six months (t24) after starting the protocol.

Regarding the retention of the participants, to ensure that there are minimal losses during the follow-up period, the researchers will make a monthly phone call to monitor pain, the current level of training, physical activity practice and if the participants sought for other methods of treatment. Participants can withdraw from the study for any reason at any time, in which case the researchers will collect the pain and function outcomes using the aforementioned instruments (if possible) and report the reasons why these patients did not complete the follow-up (Fig 1).

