## Abstract

Patellofemoral pain (PFP) is one of the most prevalent injuries in runners. Unfortunately, a substantial part of injured athletes do not recover fully from PFP in the long-term. Although previous studies have shown positive effects of gait retraining in this condition, retraining protocols often lack clinical applicability because they are time-consuming, costly for patients and require a treadmill. The primary objective of this study will be to compare the effects of two different two-week partially supervised gait retraining programs, with a control intervention; on pain, function and lower limb kinematics of runners with PFP. It will be a single-blind randomized clinical trial with six-month follow-up. The study will be composed of three groups: a group focusing on impact (group A), a group focusing on cadence (group B), and a control group that will not perform any intervention (group C). The primary outcome measure will be pain assessed using the Visual Analog Pain scale during running. Secondary outcomes will include pain during daily activities (usual), symptoms assessed using the Patellofemoral Disorders Scale and lower limb running kinematics in the frontal (contralateral pelvic drop; hip adduction) and sagittal planes (foot inclination; tibia inclination; ankle dorsiflexion; knee flexion) assessed using the MyoResearch 3.14—MyoVideo (Noraxon U.S.A. Inc.). The study outcomes will be evaluated before (t0), immediately after (t2), and six months (t24) after starting the protocol. Our hypothesis is that both partially supervised gait retraining programs will be more effective in reducing pain, improving symptoms, and modifying lower limb kinematics during running compared with the control group, and that the positive effects from these programs will persist for six months. Also, we believe that one gait retraining group will not be superior to the other. Results from this study will help improve care in runners with PFP, while maximizing clinical applicability as well as time and cost-effectiveness.

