### Participants

The eligibility criteria will be: Inclusion–(I) rearfoot striking runners with cadence under 170 steps/minute; (II) age between 18 and 45 years; (III) pain around or behind the patella, with intensity of at least 3/10 on the Visual Analogue Scale (VAS), during running and one task among squatting, climbing, and descending steps, kneeling and extending the knee with resistance [24]; (IV) being comfortable running at a speed of 10–12 km/hour. Exclusion—(I) Other disorders in the lower limbs; (II) history of surgery in the lower limbs in the last year; (III) not showing interest to adhere to a strict running retraining protocol for 2 weeks. Participants with unilateral or bilateral symptoms will be included, however, in the second case, only the worst knee (pain intensity) will be considered for analysis. The participants will be recruited through contact via e-mail, telephone, and through personnel with Goiânia’s running clubs in search of runners with PFP. In this first contact, general (gender, age, body mass, height, body mass index, history of injury and previous surgeries in the lower limbs), running (experience, volume, frequency) and pain information (intensity, location, duration of symptoms and functional tasks related to pain) will be assessed to see if the participants are eligible. Based on pain information, the diagnostic will be established using the following criteria: pain around or behind the patella during functional activities that loads the patellofemoral joint [24]. A systematic review of reviews concluded that anterior knee pain produced by functional tasks is currently the best diagnostic indicator of PFP [25]. Also, PFP is evident in 80% of the people who present anterior knee pain during a squatting manoeuvre [26].

Ethics approval was obtained from the Institutional Review Board of University of Brasilia/Faculty of Ceilândia (4.132.491), and all subjects will sign a detailed consent form before entering the study (S2–S4 Files). This study was registered in the Brazilian Registry of Clinical Trials (RBR-8yb47v) (S6 File).

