### Sample size

An a priori sample size calculation was conducted using the eta-partial square value of the group-by-time interaction for worst knee pain (0.19) obtained in a previous study that compared the effects of three gait retraining programs on runners with patellofemoral pain [27]. In G*Power software [28], we used ANOVA: repeated measures, within-between interaction, with the following parameters: effect size f = 0.48 (obtained through eta-partial square value); level of confidence = 0.05; power = 99%; number of groups = 3; number of measurements = 3. The total sample size obtained was 21 participants, however, to account for losses during the follow-up period, the final sample size will be 30 participants.

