### Data collection

Pain will be assessed using the Visual Analog Pain Scale [29], which consists of a numerical scale from 0 to 10 points, where 0 means no pain and 10 means the maximum pain ever experienced. Pain during daily activities (usual) and running will be measured. VAS is a reliable and valid scale for patients with PFP [30]. Function will be assessed using the Patellofemoral Disorders Scale [31], which contains 13 questions that assess the severity of symptoms and limitations in different activities related to PFP. It presents a score between 0 to 100 points where the lower the score the worse the function. The Patellofemoral Disorders Scale is a reliable and valid scale for patients with PFP, which has been translated into Portuguese [30,31]. The kinematics of the lower limbs will be assessed through digital videos using two webcams (MyoVideo 139 HD Color Webcam) sampling at 30 frames per second and two leds (LED Floodlight) [32]. Reflective markers will be placed on the manubrium sterni and bilateral on the anterior superior iliac spine (ASIS), greater trochanter, lateral femoral epicondyle, fibular head and lateral malleolus [33]. All participants will be instructed to run at 10–12 km/hour on a motorized treadmill (Movement XL 1600). A treadmill acclimatization period of 6 min will be used before running kinematics are measured [34]. The frontal plane camera will be placed on a portable tripod perpendicular to the frontal plane at a height of 1.30m and a distance of 2.55m from the treadmill. The sagittal plane camera will be placed on a portable tripod, perpendicular to the sagittal plane at a height of 1.15m and a distance of 2.50m from the treadmill. The video recordings will be analyzed using the software MyoResearch 3.14—MyoVideo (Noraxon U.S.A. Inc.). In the frontal plane the angles assessed will be: contralateral pelvic drop; hip adduction [33,35,36]. These angles will be evaluated during midstance. In the sagittal plane the angles assessed will be: foot inclination; tibia inclination; ankle dorsiflexion; knee flexion [33,37,38]. Foot and tibia inclination will be evaluated during initial contact while ankle dorsiflexion and knee flexion during midstance. In the frontal plane, the deepest landing position (near midstance) will be determined visually by slowly advancing the video frame by frame [33,37,38]. Since the cameras are synchronized this position will also be used to determine the midstance in the sagittal plane. Initial contact will be determined visually by slowly advancing the video frame by frame, and will be defined as the first time that the foot touched the ground [37]. To analyze the proposed angles, seven steps will be considered [33]. The study of Dingenen and colleagues [39] has found excellent inter-rater reliability (ICC) for all angles with ICC’s ranging from 0.93 to 0.99.

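### The Abstract makes pain during running the primary outcome and usual pain secondary; the Outcomes section reverses the two

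*Protocol article*

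**What the plan says.** The Abstract is explicit: "The primary outcome measure will be pain assessed using the Visual Analog Pain scale during running". It then places the other score lower: "Secondary outcomes will include pain during daily activities (usual").

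The section on outcome measures is equally explicit the other way. It says "The primary outcome of the study will be: (I) pain during daily activities (usual"), and continues: "The secondary outcomes will be: (II) pain during running".

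The Data collection section lists both scores without ranking them: "Pain during daily activities (usual) and running will be measured". The objectives in the Introduction speak only of pain. The Data analysis section names the average score on the pain scale as a dependent variable, but not which score. It sets one significance level of 0.05 and uses Sidak's method for pairwise comparisons.

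The Sample size section takes its effect from the "eta-partial square value of the group-by-time interaction for worst knee pain (0.19") of an earlier study. The Participants section requires pain "with intensity of at least 3/10 on the Visual Analogue Scale (VAS), during running and one task among squatting" and several other knee-loading tasks. It sets no minimum for usual pain.

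**The concern.** A single primary outcome fixed in advance is what allows one test at 5% to carry the trial's conclusion. Here there are two candidates, each named as primary in one part of the same document. If the two scores gave different answers, a report built on either could cite this article as its pre-specification. The plan has no other safeguard across outcomes, since the stated adjustment concerns comparisons between groups within an outcome.

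The choice also matters for what the trial can show. The two scores have different entry conditions, and the sample size is justified on a pain measure that the text does not identify with either of them.

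**Working it through.** **1. The designations side by side**

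| Section | Pain during running | Usual pain |
|---|---|---|
| Abstract | primary | secondary |
| Outcomes measures | secondary | primary |
| Data collection | measured, not ranked | measured, not ranked |
| Data analysis | pain scale named, score not specified | pain scale named, score not specified |
| Sample size | not named (worst knee pain) | not named (worst knee pain) |

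The first two rows are an exact swap. The other rows do not decide between them.

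**2. Error rate if either score may be called primary**

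Inputs: two outcomes, each tested at 0.05 (Data analysis). Under independence, 1 − (1 − 0.05)² = 1 − 0.9025 = 0.0975. Two pain scores from the same knee are probably positively correlated, which brings the figure down towards 5%. The documents give no correlation, so the range is 5% to about 9.75%.

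**3. The stated sample size, reproduced**

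Inputs from the Sample size section: partial eta squared 0.19, f = 0.48, alpha 0.05, power 99%, 3 groups, 3 measurements. Assumed because not stated: correlation between repeated measures 0.5 and sphericity (epsilon = 1), the software defaults.

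- f = √(0.19 / 0.81) = 0.484, given as 0.48.
- Noncentrality = f² × N × m / (1 − ρ) = 0.2304 × 21 × 3 / 0.5 = 29.03.
- Degrees of freedom: (3 − 1)(3 − 1) = 4 and (21 − 3)(3 − 1) = 36.
- Power at N = 21 is 0.990; at N = 18 it is 0.973. The stated 21 is therefore reproduced.
- 21 / 30 = 0.70, so the final 30 allows for 30% losses.

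The arithmetic is sound, but its effect size belongs to worst knee pain. The documents give none for running pain or usual pain, so no corrected sample size can be computed. For illustration only, under the same assumptions:

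| f | Power, N = 21 | Power, N = 30 |
|---|---|---|
| 0.48 | 0.99 | over 0.99 |
| 0.40 | 0.94 | 0.99 |
| 0.35 | 0.85 | 0.97 |
| 0.30 | 0.71 | 0.89 |
| 0.25 | 0.53 | 0.73 |

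**4. Entry conditions**

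The pain scale runs from 0 to 10. Eligibility guarantees running pain of at least 3 at entry. For usual pain, a starting value of 0 is permitted.

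**The case against.** The best defence is that the Outcomes section is the operative part of the Methods and, read alone, names exactly one primary outcome; the Abstract could simply be a slip. The protocol also cites a prospective registration, not shown here, which may fix the matter. Both points are fair, and they limit the error-rate consequence: it arises only if nothing outside this article binds the choice. They do not remove the contradiction. Condensing a protocol into an article can drop detail, but it does not reverse primary and secondary.

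Some stronger readings are tempting and should be resisted:

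- A reader might infer that the trial was sized on a third outcome that it does not measure, so that the power statement is void. The text does not establish this. The Participants section uses similar wording for the more painful knee in bilateral cases, so worst knee pain may mean pain in the worse knee. In any case, borrowing an effect from a related pain measure is a mismatch to disclose, not an error in itself.
- A reader might infer that floor effects will dilute a treatment difference in usual pain. No baseline distribution is given. The qualifying tasks include stairs, squatting and kneeling, which are largely everyday activities, so very low usual pain may be uncommon. The floor is a possibility, no more.
- Because the six-month comparison is the secondary objective, a reader might want to make the two-week assessment alone decisive. That would replace the three-time-point group-by-time interaction on which N = 21 rests, and is a larger change than this defect calls for.

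**Conclusion.** The point stands as an internal contradiction that must be corrected: the Abstract and the Outcomes section name different primary outcomes, and no section shown reconciles them. The consequence for error control is a false-positive chance of up to about 9.75%. That figure assumes independent scores and a free choice between them; positive correlation or a binding registration would reduce it.

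The sample size mismatch is a secondary note. The stated 21 is correct for its inputs under the software defaults, but the 99% power is not shown to apply to running pain or to usual pain. How far it might fall cannot be derived from the documents.

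**What to change.** Before outcome data are seen, name one pain measure as primary, in identical words, in the Abstract, Outcomes, Sample size and Data analysis sections, and make the other secondary. Follow the prospective registration if it settles the matter. If it does not, running pain is a reasonable choice: eligibility gives it a minimum of 3/10 and so room to improve, whereas usual pain may start near 0.

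Keep the planned group-by-time analysis over the three assessments. Add a sentence to the Sample size section saying that partial eta squared 0.19 (f = 0.48) comes from worst knee pain in an earlier study, what that measure was, and why it is taken to apply to the chosen outcome.

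The cost is wording in four sections and an amendment note. The number of participants, the assessments and the model are unchanged.
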